## Abstract

**Background:**

Physical activity not only is beneficial to a person’s health, but can also have a positive influence on cognitive functioning. However, elderly people with chronic illness(es) often do not meet the physical activity guidelines. Physical activity programs for the elderly exist, but these are often expensive and not easily accessible to the elderly with chronic illness(es). In addition, the beneficial effects of these physical activity programs on cognitive functioning have never been specifically tested in this target group. Hence, this randomized controlled trial aims to test whether Active Plus, a proven effective physical activity intervention, is able to improve the cognitive functioning of elderly people with chronic illness(es) or to slow down cognitive decline. In addition, it studies what kind of activity, intensity, duration and frequency of physical activity most strongly influence cognitive functioning.

**Methods:**

A randomized controlled trial is performed, comparing the Active Plus intervention group to a waiting list control group. In total 540 older adults (≥65 years) with at least one chronic illness that limits mobility are recruited from 7 municipalities. Comparable neighborhoods within a municipality are randomly allocated to the intervention or control group. Baseline and follow-up measurements after 6 and 12 months assess cognitive functioning and physical activity behavior, measured both objectively with an accelerometer and subjectively with a self-report questionnaire. Multilevel analyses are conducted to assess effects on cognitive functioning, including analyses on moderation effects for physical activity type, frequency, duration and intensity.

**Discussion:**

To our knowledge this is the first study to investigate effectiveness of a physical activity program on cognitive functioning in elderly people suffering from a broad range of chronic illnesses. If proven effective Active Plus would be a very cost effective intervention not only to increase physical activity, but also to improve cognitive functioning or slow down cognitive decline. Up till now clear evidence is lacking on the kind of physical activity, intensity, duration and frequency needed to achieve cognitive benefits. By measuring both with accelerometers and self-report questionnaires we hope to gain insight in these processes.

**Trial registration:**

Nederlands Trial Register NL6005; Date of Registration 21-03-2017.

## Background

Chronic illnesses in elderly people have a major impact on society. The older a person becomes, the more likely they develop one or more chronic illnesses, such as cardiovascular disease, osteoarthritis and diabetes [1–4]. These chronic illnesses are associated with, among others, depressive symptoms, cognitive functioning problems, and mobility limitations [5–7]. Eighty percent of the elderly population living in developed countries suffer from a chronic illness and 50–75% have to deal with multiple chronic illnesses [4, 8, 9]. Therefore, the demand for healthcare among elderly people is large and will increase even further in the future due to the aging world population [3]. Most countries experience growth in the number and proportion of older people in their population. The number of people aged 65 years or over is expected to nearly triple by 2050, rising from 542 million globally in 2010 to about 1.5 billion in 2050 [10]. More importantly, worldwide the population aged 60 or over is growing faster than all younger age groups. Since the number of elderly people increases and the potential labor force remains the same or even declines, the costs of health care will increase [11].

Chronic illnesses in the elderly not only have a major impact on society, but also on their individual degree of independence and quality of life [12]. Elderly people may suffer not so much from the illnesses themselves, but from the limitations as a result of these chronic illnesses [13]. These limitations, such as mobility restrictions, stand in the way of an independent life and can lead to loneliness [14]. Consequently, the World Health Organization [15] focuses its policy framework on active aging by which chronic illnesses and reduced mobility should be prevented on the one hand, and vitality, self-reliance, participation in society and quality of life should be optimized on the other hand [3]. This should culminate in elderly people living independently for as long as possible; and good health is a prerequisite for this [16]. The functioning of the elderly can be optimized by a change in lifestyle, of which physical activity (PA) is an important component [3].

Engaging in regular PA has great health benefits [17]. It is effective in controlling weight, strengthening muscles and bones, improving mood and the ability to do daily activities and preventing falls. Additionally, there is indisputable evidence of the effectiveness of regular PA in the prevention of several chronic diseases (e.g., cardiovascular disease, diabetes, cancer, hypertension, obesity, depression and osteoporosis) and premature death [18].

Furthermore, there is preliminary evidence to suggest that PA is beneficial for cognitive functioning (CF). An increasing number of scientific studies show that PA has a positive influence on CF in general [19]. However, not all PA programs show this result [20, 21]. In the aging brain, sufficient PA correlates with a reduced risk for cognitive decline [22]. Several review articles state that executive functions appear to benefit most from PA [23–25]. Executive functions are higher-order cognitive processes that are necessary to control cognitive behavior. These processes include planning, working memory, inhibition, mental flexibility, as well as the initiation and monitoring of action [26]. Without these functions, well-organized behavior is not possible. However, the underlying mechanisms on how PA may protect against cognitive decline are still somewhat unclear, although elevated neurotrophin levels, improved vascularization, facilitation of synaptogenesis, decreased systemic inflammation, and reduced disordered protein deposition may play a role [19]. Studies have shown that adding any moderate intensity PA program in later adulthood is beneficial for cognitive performance, especially for very sedentary older adults [27]. All things considered, by engaging in regular PA, one can therefore actively contribute to a healthy brain.

Notwithstanding the increasing body of evidence for the importance of regular PA, most elderly people do not reach the recommended guidelines [28]. These guidelines state that adults should be active for at least 150 min at a moderate-intensity spread over a few days per week and perform resistance training at least 2 days per week. Data from the U.S. Department of Health and Human Services indicate that more than 80% of adults do not meet these guidelines for both aerobic and muscle-strengthening activities [29]. Comparable numbers are shown in a study in the Dutch population; only 33% of the elderly of 65 years or over meet the guidelines [30].

Within the elderly population those with chronic illnesses are most sedentary and perceive many PA related barriers [31]. Although a few PA programs exist for elderly with chronic illnesses (e.g. Coach2Move [32], Strong-for-Life [33], Life-P [34]) most programs are not easily accessible, often not attended by elderly with chronic illnesses and often only reaching already active elderly [35]. Moreover, the programs are often face-to-face and high demanding [36].

Active Plus is an existing proven effective personalized PA program for elderly people which provides the target group with 3 personalized PA advices (online and print delivered) in 4 months [37]. Preceded by a questionnaire (e.g. on current PA and perceived PA beliefs and barriers) a computer-tailoring program generates personalized advice, tips and exercises that are sent to the user. Active Plus raises awareness of PA, and guides PA initiation and maintenance. The program is tailored to patient and disease specific situations and needs [38]. Previous research in a general population of people aged over 50 years showed in the Active Plus group in 1.5 h per week more moderate to vigorous intensity PA after 1 year compared to controls [37, 39, 40], even in elderly people with limited mobility [41, 42]. Active Plus is highly cost-effective, reduces disease incidence and potentially reaches many elderly people with a chronic illness and limited mobility at very low costs [43–45].

As the program Active Plus has strong indications for long-term effects on moderate to vigorous PA in the elderly with chronic illnesses and limited mobility, we hypothesize that Active Plus improves cognitive functioning in this target group. In a meta-analysis and systematic review on effects of exercise on cognitive function in chronic disease patients by Cai [46] a positive overall effect of exercise interventions on cognitive function was found. However, 22 out of 35 included studies only included patients with Alzheimer’s disease or Mild Cognitive Impairment. Other included studies targeted their intervention to only one individual chronic illness (i.e. cancer, heart failure). To our knowledge, the effects of PA on CF in an elderly population which suffers from a broad range of chronic illness(es) have not yet been tested. Furthermore, the interventions included in the meta-analysis were site-situated, which is high demanding, more expensive, and mainly focused on exercise, while a computer-tailored PA intervention like Active Plus has a strong focus on stimulating daily PA [35, 36]. Therefore, the primary objective of the present Active Plus study is to investigate the short-term (6 months) and long-term (12 months) effects of the Active Plus program on CF of people aged 65 years or older with chronic illness(es) through a clustered randomized controlled intervention trial (RCT). This paper describes the protocol for this objective and the other objectives below.

PA is complex behavior consisting of type of activity, duration, frequency, and intensity [47]. There are some indications that the beneficial effects of PA on CF are independent of these characteristics of PA [46]. However, another meta-analysis [48] showed that only a duration of > 45 min to ≤60 min per session at a moderate-to-vigorous intensity on as many days per week was beneficial for CF. Therefore, it is unclear what characteristics PA should have to be effective on CF in clinical practice. To provide more insight in this matter, we will study as another primary objective the relationship between the necessary type, frequency, duration and intensity of PA to increase CF or slow down its decline in the elderly with chronic illness(es) (ECI). To test PA behavior, we use both self-report questionnaires and accelerometers. Self-report questionnaires are known for overestimating PA, however they measure different constructs than accelerometers [49]. Therefore, both ways of measuring PA are administered in this project.

As mentioned before, elderly people with chronic illnesses have a lesser individual degree of independence and quality of life [12], and experience more feelings of loneliness [14]. Sufficient levels of PA and CF are important for self-reliance and a good health related quality of life (HRQoL) [3]. However, being sufficiently physically active is a great challenge for this target group [31]. Therefore, a secondary objective is to study the effects of the Active Plus intervention on self-reliance, HRQoL and loneliness.

## Methods

### Study design

The study is a parallel, two-group cluster-RCT with a waiting list control group and assessments at baseline, six and 12 months. Due to the nature of the study, it is not possible to blind the researchers. Participants do not know there are two groups being examined. Ethical approval for the study was obtained from the Research Ethics Committee (cETO) of the Open University and the trial is registered with the Dutch Trial Register, protocol number NL6005. This protocol is reported in accordance with SPIRIT guidelines. The study is funded by a grant from the Brain Foundation Netherlands. All participants provide written informed consent prior to commencing the study. Participants may withdraw from participation at any time without giving an explanation, no data will be collected anymore. There are no interventions or care prohibited during the trial.

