**Fig. 1 Fig1:**
[figure not shown]
Schematic overview of the randomized controlled trial procedure and the intervention

Before the CF test, participants in both groups receive an accelerometer device by mail with an explanation on how and when to wear it. They are asked to wear it for 7 consecutive days on their right hip. The day after the last wearing day they are visited at home by a researcher (assistant) or student who brings the accelerometer back to the research institute.

The CF tests are assessed by a trained researcher or student on an iPad Air 2 at the participants’ home with Inquisit 5 software [51]. To become familiar with the iPad, participants are asked to draw a house and a tree in the Notes application. The CF tests start with the first part of the 15 Words Learning Task, a Dutch adaptation of the Rey’s Verbal Learning Task, followed by the Trail Making Test part A and B, the Stop Signal Task, and the Letter Digit Substitution Task. The test ends with the second part of the 15 Words Learning Task. The total test takes around 45 min to complete. Any occurring disturbances or difficulties in completing the test are administered. For more information on the CF tests see the outcome measures section.

After the CF test participants choose to complete the baseline questionnaire online on www.actief-plus.nl or on paper (with a prepaid return envelope). Thereafter, the 4 month lasting intervention commences for the experimental group. After 6 months and 12 months participants are contacted again to make an appointment for the second and third measurement. They wear the accelerometer device again, are visited at home to take the cognitive tests and complete a questionnaire. Procedures for the second and third measurement are similar to the first measurement. After the final assessment participants in the control group receive access to the Active Plus intervention.

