#### Experimental condition

The computer tailored Active Plus intervention stimulates PA among people aged 65 or over with a chronic illness and is proven to be effective in increasing PA behavior [37, 42–45]. The intervention is systematically developed using the Intervention Mapping Protocol, and based on various theoretical models such as the Theory of Planned Behavior [52], Precaution Adoption Process Model [53], the Integrated Model for Change (I-Change Model) [54], and a self-regulation model [55]. The intervention intents to take up and sustain PA behavior by influencing (pre−/post-) motivational constructs. The pre-motivational constructs addressed are awareness and knowledge among others. Constructs such as intention, social influence, intrinsic motivation, attitude and self-efficacy are addressed in the motivational stage. Post-motivational constructs include action planning, coping planning, strategic planning, commitment, and self-regulation skills. Especially for the targeted population of ECI tailored information is added on several chronic illnesses, the risks of sedentary behavior, and the benefits of PA for CF.

Participants in the experimental group receive advice on three occasions (see Fig. 1), tailored to the answers they give in questionnaires. The first personal advice is delivered right after the baseline assessment. Participants receive the second advice 2 months after the baseline questionnaire. And within 4 months after the baseline questionnaire feedback on progress in PA behavior is given, based on the second assessment (only used to generate a third advice). All participants in the experimental condition receive a copy of their personal advises by email (if they have registered an email address) and by mail as well. Participants receive an invitation for the follow-up assessment by mail, together with the follow-up questionnaire and a prepaid return envelope, and by email, including a link to the questionnaire.

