#### CF outcomes

The Verbal Learning Test (VLT) [56] is a frequently used measure of verbal memory. Several studies found PA interventions effective in improving memory [19]. As memory complaints are often the first cognitive complaints people suffer from this aspect of cognitive functioning is also included in the current study. In this test, 15 words are presented one by one on an iPad screen in fixed order, with a presentation time of 1 s and an interstimulus interval of 1 s. Afterwards participants are asked to verbally recall the words they have remembered. The first trial is followed by four more trials in which the words are presented in identical order. After a delay of 15–25 min in which the remaining CF tests are assessed, and unexpectedly for the participants, the instruction is given to recall the 15 words learned once more. Finally, a recognition trial is administered. Greater test scores indicate better verbal memory.

The Letter-Digit Substitution Test (LDST) [57] is a modification of the procedurally identical Symbol-Digits Modalities Test [58]. This test is often used as a measure of processing speed of general information, which is found to be affected by PA [20]. In the LDST, letters are presented and the participant has to respond by clicking the corresponding digits, according to a key. After a practice round of 10 letters, the participant has 60 s to replace the randomized letters with the appropriate digit indicated by the key. Greater test scores indicate better speed of information processing.

The Trail Making Test (TMT) provides information on visual search, scanning, speed of processing, mental flexibility, and executive functions [59]. The TMT consists of two parts. TMT-A requires the participant to draw lines with their finger sequentially connecting 25 encircled numbers distributed on the iPad. Task requirements are similar for TMT-B except the participant must alternate between numbers and letters (e.g., 1, A, 2, B, 3, C, etc.). The score on each part represents the amount of time required to complete the task. Score on B-A is a measure for shifting, which is a construct of executive functioning and is found to be affected by PA [60]. The larger the score B-A is, the more difficulty the participant has with shifting.

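### The statement that researchers cannot be blinded is not justified for the home testers of cognitive functioning, and it leaves an avoidable risk of detection bias

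*Protocol article*

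**What the plan says.** Under Study design, the protocol article says of blinding: "Due to the nature of the study, it is not possible to blind the researchers". The next sentence concerns participants: "Participants do not know there are two groups being examined". Outcome testers are not treated separately.

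Under Procedure, testing is done in person at the participant's home: "The CF tests are assessed by a trained researcher or student on an iPad Air 2". The tester also notes any disturbance or difficulty during the test and takes the accelerometer back. Testing is repeated at 6 and 12 months: "Procedures for the second and third measurement are similar to the first measurement".

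The intervention takes another route. Under Background, "a computer-tailoring program generates personalized advice, tips and exercises that are sent to the user". Under Experimental condition, "All participants in the experimental condition receive a copy of their personal advises by email (if they have registered an email address) and by mail". A website carries the rest of the content.

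Under Outcomes, CF and physical activity (PA) are both primary. Of the four CF tests, the VLT is the one with a spoken response: "Afterwards participants are asked to verbally recall the words they have remembered".

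**The concern.** The article rests the lack of blinding on the nature of the study. That is a sound reason where the person who measures the outcome also delivers the treatment, or where the treatment is visible at the visit. Neither is described here. The people who go to the homes give tests, and the treatment is sent by a computer system.

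If testers know the arm and the hypothesis that Active Plus improves CF, expectation can affect how instructions are given, how a doubtful spoken word is credited, and what is noted as a disturbance. A systematic difference of this kind cannot be separated from a treatment effect in the analysis, so it has to be prevented at the visit. The planned effect is modest (0.30), so even a small shift would matter.

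**Working it through.** The protocol gives no figure for assessor bias, so the main check sets its statements side by side. The arithmetic that follows is an illustration.

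**Does the stated reason cover the testers?**

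1. *Delivery.* Advice is generated by software and sent by email and post, with a website (Background; Experimental condition). No section gives a tester a part in this.
2. *Testing.* One procedure is described for both groups, and the follow-up visits repeat it (Procedure). Nothing in it requires the tester to know the arm.
3. *Participants.* They are said not to know that two groups exist (Study design). A control participant has received no advice to mention.
4. *Result.* The stated reason may hold for staff who run the tailoring system. It does not explain why a visiting tester must know the allocation.

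**Where could a tester influence the score?**

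| Primary measure | How the score arises | Room for tester influence |
|---|---|---|
| VLT | spoken recall; scorer not stated | crediting of words (if the tester scores), administration |
| Letter-Digit Substitution Test (LDST) | participant's clicks in 60 s | administration only |
| Trail Making Test (TMT) | completion time on the tablet | administration only |
| Stop Signal | stop signal reaction time estimated from an adaptive task | administration only |
| PA | accelerometer and self-report questionnaire | not a CF test; outside this point |

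**How much would a small shift matter? (illustration)**

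Inputs from Sample size and statistical power: effect size 0.30, ICC 0.01, 190 per group after dropout. The 190 agrees with the 270 to be included: 190/(1 − 0.30) = 271.4. It is used here as stated.

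Assumptions: outcome in SD units, two-sided 5% test, true effect zero, and a tester-induced difference *b* in favour of one arm. For clustering, one cluster per arm in each of the seven municipalities is assumed.

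- Without clustering: SE = √(2/190) = 0.103.
- With clustering: *m* = 190/7 = 27.1; design effect = 1 + (27.1 − 1) × 0.01 = 1.26; SE = 0.103 × √1.26 = 0.115.
- False-positive rate = 1 − Φ(1.96 − *b*/SE) + Φ(−1.96 − *b*/SE).

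| Assumed *b* (SD) | Share of 0.30 | Rate, SE 0.103 | Rate, SE 0.115 |
|---|---|---|---|
| 0.05 | 17% | 7.8% | 7.2% |
| 0.10 | 33% | 16.4% | 14.0% |
| 0.20 | 67% | 49.6% | 41.1% |

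The table shows sensitivity. It does not estimate what would happen in this trial.

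**The case against.** The strongest reply is that masking would be fragile here. Allocation is by neighbourhood and testing is at home, so the address identifies the unit of allocation to anyone who knows or infers the list. By the 6-month visit, experimental participants should have received three advices, with paper copies. One remark could unmask a whole area. This stands, and it rules out any claim that testers can be kept fully unaware. It does not make withholding the list pointless, since an address reveals the arm only to someone who can connect the two.

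A second reply is that most of the CF battery leaves little to the examiner. This also stands. Three of the four tests are scored from the participant's own responses or timing, and the protocol does not say who scores the VLT. That the tester counts the words is an inference.

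A third reply is that a remedy could damage a safeguard already in place. Asking participants not to mention advice they have received would suggest to the waiting-list group that others receive advice. This is right, and the fix must respect it.

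Finally, this is a condensed article, and tester instructions belong in fuller documents. That would answer a complaint about silence. Here the article states that blinding is impossible, which is a position of its own.

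A reader might infer that masking costs nothing. The documents do not support this: they do not say who runs the tailoring software, who makes the follow-up appointments, or how many testers there are.

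**Conclusion.** The point holds as a risk that the plan could reduce cheaply. The statement on blinding is too broad: the nature of the study, as described, does not explain why the home testers of a primary outcome must know the arm. The exposure is mainly in the VLT and in face-to-face administration, and smaller in the LDST, TMT and Stop Signal tasks.

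A reader might go further and conclude that detection bias does enter the primary endpoint, in favour of Active Plus. The documents do not show this. They do not report that any tester acted on knowledge of the arm, and they do not say outright that every student tester knows it. They say that researchers cannot be blinded and plan no exception. CF is also not the only primary outcome.

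Nor can a size be given. One could take half a word of leniency against an SD of 3 words and obtain 0.5/3 = 0.17 SD, but neither figure is in the protocol, and the result would concern the VLT alone. The false-positive rates above, about 7% to 50% for shifts of 0.05 to 0.20 SD, depend wholly on the assumed shift, a two-sided 5% test and seven clusters per arm.

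**What to change.** Limit the blinding statement to staff who run the tailoring system, and add a short rule for the 6- and 12-month visits:

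- The existing testers do not receive the allocation list.
- Each tester is scheduled for visits in both arms.
- After each visit the tester records a guess of the arm, and the agreement with the true allocation is reported.
- Whether a disturbed test is valid is decided before allocation is linked to the data.
- Any request to participants is neutral and identical in both arms, for example not to talk about study materials during the test, so that it does not reveal that two groups exist.

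The cost is some scheduling work, a line in the tester instruction, and keeping the allocation list away from those who visit. Sample size, instruments and intervention stay as they are. Some unmasking through the neighbourhood or participants' remarks will remain and should be reported as a limitation.
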